## Background

Acute stroke in pregnancy and puerperium (ASPP) is a rare but serious complication associated with high morbidity and mortality in women of childbearing age. The incidence of pregnancy-associated stroke is estimated at 30 per 100,000 pregnancies and appears to be rising, with an inhospital mortality rate of 4.2% for pregnant women experiencing acute stroke [1–3]. Compared to their nonpregnant counterparts, pregnant women with acute stroke face a higher risk of deterioration and more complex management needs [4]. Regarding the long-term risk of ASPP, women with pregnancy-associated stroke have lower risks of recurrent ischemic stroke and mortality compared to those with strokes unrelated to pregnancy. Furthermore, the risks of recurrent intracerebral hemorrhage and cerebral venous thrombosis do not differ significantly, and recurrent stroke during subsequent pregnancies remains rare [5].

Previous studies have predominantly utilized large-scale national healthcare data and the International Classification of Diseases (Tenth Revision, Clinical Modification) (ICD-10-CM) to examine the incidence rate and risk factors for ASPP [6–8]. Although these population-based studies benefit from larger sample sizes, they often lack detailed data, which hinders a comprehensive exploration of risk factors and the identification of prognostic predictors and range of variables collected, such as laboratory results, neuroimaging characteristics, and management strategies. This limitation hampers the comprehensive exploration of risk factors and the identification of prognostic predictors. As women with ASPP are generally young and likely to achieve good recovery, no long-term follow-up studies have been conducted to assess their long-term functional outcomes. Additionally, it remains to be explored whether ASPP is solely a short-term risk factor that does not affect a woman’s risk of stroke in future pregnancies or throughout her life.

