## Methods

### Design

This is a retrospective, observational, nationwide, multicenter study divided into three parts. The first part is a case-control study aimed at identifying the risk factors of ASPP and its prognostic predictors. The second part is a cohort study to evaluate the impact of ASPP on the risk of recurrent stroke. The third part is a cohort study to assess the impact of ASPP on the prognosis of their offspring.

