### Data collection and management

Baseline data collection will be conducted through the electronic medical record (EMR) system of the participating centers. If certain variables are not recorded in the EMR, they will be collected retrospectively through telephone interviews. Table 2 presents the variables to be collected at baseline. A specialized secure database (CRF, case report form) will be established to facilitate the collection of standardized data from different centers. All data will be anonymized to ensure privacy, and each patient included in this study will be identified by an identity number. General variables (such as demographics, medical history, and medication history) and pregnancy- or puerperium-associated variables (including data on delivery and offspring-related variables) will also be collected for non-ASPP participants.

**Table 2 Tab2:** Baseline variables

• **Demographics**
▪ Age
▪ Ethnic: Han or other
• **General clinical variables**
▪ Date of admission and discharge
▪ BMI (calculated based on prepregnancy weight and height data)
▪ Previous or current smoking
▪ Previous or current drinking
▪ Previous or current drug abuse
▪ NIHSS and/or mRS at admission and discharge
▪ Blood routine index: RBC, WBC, PLT, etc.
▪ Blood biochemical index: TC, HDL-C, etc.
▪ Coagulation function index: TT, PT, FIB, APTT, etc.
▪ Other blood index: lupus anticoagulant, anticardiolipin antibodies, etc.
• **Medical history**
▪ Hypertension (if with record maximal SBP and DBP)
▪ Diabetes
▪ Migraine
▪ Polycystic kidney disease
▪ Cerebral vascular disease (if with record etiology)
▪ Myocardial infarction or angina
▪ Congestive heart failure
▪ Known atrial fibrillation or flutter
▪ Valvular heart disease
▪ Hypercholesterolemia
▪ Pulmonary embolism

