### Statistical analysis

Descriptive statistics will express continuous variables as means (±standard deviation) or medians (interquartile range) and categorical variables as proportions. Chi-square tests or Fisher’s exact tests, along with Student’s *t*-tests or Wilcoxon rank-sum tests, will be used to compare demographics and clinical characteristics between cases and controls. Chi-square tests will compare dichotomous outcomes, while *t*-tests or Mann-Whitney *U*-tests will compare quantitative outcomes. Kaplan-Meier curves and log-rank tests will evaluate survival analyses, with Cox proportional hazard models calculating hazard ratios and 95% confidence intervals (CIs). Multivariate logistic regression will identify independent predictors, and linear or generalized linear models will assess the impact of ASPP and other factors on delivery outcomes and the ASQ-3 results. First, logistic regression will calculate odds ratios and 95% CIs for recurrent stroke. Subgroup analysis will evaluate potential differences in endpoints for predefined subgroups (such as gestational hypertension, preeclampsia, HELLP syndrome, gestational diabetes, trimester, and type of delivery). Multiple imputation will address missing baseline data, with a *p*-value of < 0.05 considered statistically significant.

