The findings of this study should be interpreted within the context of potential limitations. Firstly, this is a retrospective study, which is subject to several inherent biases, such as recall and information bias, potentially jeopardizing its validity. Secondly, follow-up via telephone interviews may lead to a high dropout rate. Thirdly, concerns among ASPP patients regarding the privacy of their offspring’s information may result in a significant number being unwilling to cooperate, leading to selection bias. To address these issues, expanding the sample size by including more centers would be an effective solution for achieving statistical validity. Finally, although this study focuses on the Chinese population and mainly includes the Han ethnic group as the primary ethnic cohort, it employs two methodological measures, geographical heterogeneity and biological consistency, to ensure the generalizability of the research findings. The study included 22 provinces representing different socio-economic and medical resource conditions to ensure geographical heterogeneity. According to previous national studies, in the Chinese population, the key risk factors for ASPP, such as hypertension and coagulation dysfunction, show minimal differences across different ethnic groups, suggesting that the study subjects have biological consistency [24, 25].

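### Antiphospholipid tests come from routine records and missing results are to be imputed, so any Aim 1 odds ratio for them against stroke-free pregnant controls is open to ascertainment bias

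*Protocol article*

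**What the plan says.** The Design section makes Aim 1 a case-control comparison: "The first part is a case-control study aimed at identifying the risk factors of ASPP and its prognostic predictors". One of its two control groups is stroke-free pregnant or postpartum women, matched 1:1 to cases on age and hypertension history.

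On the source of the data, Data collection and management states: "Baseline data collection will be conducted through the electronic medical record (EMR) system of the participating centers". The fallback is: "If certain variables are not recorded in the EMR, they will be collected retrospectively through telephone interviews". Table 2 then lists, under the general clinical variables, "Other blood index: lupus anticoagulant, anticardiolipin antibodies, etc".

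For participants without ASPP, the same section says that two kinds of variable are also collected: "General variables (such as demographics, medical history, and medication history) and pregnancy- or puerperium-associated variables". The examples do not name blood tests, but the word general echoes the Table 2 heading under which the blood tests stand.

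The Background faults earlier studies for lacking detail "such as laboratory results, neuroimaging characteristics, and management strategies", and says that this hampers the search for risk factors and for prognostic predictors. Statistical analysis compares clinical characteristics between cases and controls, uses multivariable logistic regression to find independent predictors, and gives one rule for gaps: "Multiple imputation will address missing baseline data".

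**The concern.** A case-control odds ratio needs the exposure to be ascertained in a comparable way in both groups. Age, BMI or a routine blood count is recorded whether or not a woman has a stroke. An antiphospholipid test is different: it exists in the record only if someone ordered it. A stroke is a plausible reason to order it, whereas a stroke-free pregnant woman would need some other indication.

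The missing value then means that the test was not ordered, and the reason for not ordering is tied to case status. Multiple imputation does not repair this by itself. If the imputation model contains case status, control values are drawn from the few controls who were tested. If it does not, they are drawn largely from cases. Neither source need represent the untested controls.

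At stake is whether the study reports a thrombophilia factor as raising or lowering the risk of ASPP when the figure mainly reflects who was tested.

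**Working it through.** The article gives no figure on this point, so there is nothing to reproduce. The check sets out what is fixed and then illustrates how far an odds ratio (OR) could move.

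**Inputs from the article**
- 400 cases and 400 stroke-free pregnant controls (abstract).
- Existing records as the source, telephone interview as the fallback, and no required testing.
- The key data whose absence excludes a participant (Table 1) do not name blood tests, so untested women stay in.
- Multiple imputation for missing baseline data.

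**Assumed inputs, not in the article**
- True prevalence *p* = 3% in both groups, so the true OR is 1.
- Testing rates *t*₁ in cases and *t*₀ in controls of 70%/10%, with 80%/20% and 50%/5% as the range.
- Where controls are tested for an indication, 6% to 10% of tested controls are positive.

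**(a) Untested counted as negative.** OR = [*pt*₁/(1 − *pt*₁)] / [*pt*₀/(1 − *pt*₀)].
- 70%/10%: (0.021/0.979) / (0.003/0.997) = 7.1
- 80%/20%: (0.024/0.976) / (0.006/0.994) = 4.1
- 50%/5%: (0.015/0.985) / (0.0015/0.9985) = 10.1

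**(b) Tested women only, tested controls enriched.**
- 6% positive: (0.03/0.97) / (0.06/0.94) = 0.48
- 10% positive: (0.03/0.97) / (0.10/0.90) = 0.28

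**(c) Multiple imputation, the rule the plan states.** If the model contains case status and nothing else that explains why controls were tested, imputed controls have on average the prevalence of the tested controls. The expected result is that of (b), 0.48 to 0.28. If the model omits case status, imputed values take the pooled prevalence of all tested women. With 280 of 400 cases and 40 of 400 controls tested:
- 6% positive: pooled = (280 × 0.03 + 40 × 0.06)/320 = 3.375%. Cases become (8.4 + 120 × 0.03375)/400 = 3.11%, controls (2.4 + 360 × 0.03375)/400 = 3.64%, OR = 0.85.
- 10% positive: pooled = (8.4 + 4)/320 = 3.875%. Cases become 3.26%, controls 4.49%, OR = 0.72.

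The second version looks milder only because the true OR here is 1. Giving untested controls largely the cases' prevalence would also pull a real association towards 1.

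**(d) Tested women only, testing unrelated to antibody status.** The expected OR is 1.0, so there is no bias. The cost is precision. Take 5% prevalence and 320 tested cases (16 positive, 304 negative):
- All 400 controls tested: SE(log OR) = √(1/16 + 1/304 + 1/20 + 1/380) = 0.34
- 5% of controls tested (20 women, 1 expected positive): SE(log OR) = √(1/16 + 1/304 + 1/1 + 1/19) = 1.06

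A 95% interval multiplies and divides the estimate by exp(1.96 × SE): about 2 in the first case and about 8 in the second.

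**The case against.** **No such odds ratio is announced.** Table 2 is a collection list, Statistical analysis names no candidate variables, and Aim 1 also covers prognostic predictors within cases, which this difference between groups does not touch. Moreover, the examples given for women without ASPP do not include blood tests. If they are not collected in controls, no odds ratio against stroke-free controls exists. This stands, and it makes the point conditional. It does not remove it: the tests sit under the general clinical variables, and laboratory detail is presented as helping the search for risk factors.

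**Testing rates are unknown.** A reader might infer that the article shows most cases and few controls to be tested. It gives no testing rate and no indication for testing in either group; unequal testing is an inference from the design.

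**An odds ratio near 7 is not the plan's expected result.** It belongs to counting untested women as negative, a rule the plan does not adopt. It shows sensitivity to coding and is no forecast.

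**Not every way of handling the gap is biased.** Analysing tested women only is unbiased when testing is unrelated to antibody status, as (d) shows.

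**The Discussion does not single out antibodies.** It mentions "the key risk factors for ASPP, such as hypertension and coagulation dysfunction", but that sentence concerns similarity across ethnic groups and adds nothing about antiphospholipid tests.

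**Candidate lists and imputation models usually belong in an analysis plan.** That is true, and their absence here is not the point. The article does state a rule for missing baseline data, and as worded the rule covers results missing because no test was ordered. The Discussion concedes information bias in general terms, but its proposed remedy of more centers would add precision without removing bias.

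**Conclusion.** The concern holds in conditional form. If lupus anticoagulant and anticardiolipin antibodies are collected in stroke-free pregnant controls and handled under the stated imputation rule, their Aim 1 odds ratios are open to ascertainment bias of uncertain direction and are at best very imprecise. If they are not collected in those controls, the article should say so.

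The size cannot be derived from the article. With a true odds ratio of 1, the illustrations run from about 0.3 to about 10 depending on coding and on why controls were tested, all on assumed testing rates and prevalence. The documents do not support saying that the bias will occur, that it has a known direction, or that a false thrombophilia finding is the likely result.

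The point concerns the stroke-free pregnant controls only. Women in the nonpregnant stroke group also have a stroke to prompt testing, and prognostic analyses within cases are unaffected by this difference. No primary outcome is involved, but the rule should be settled before analysis.

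**What to change.** In Statistical analysis:
- Limit the risk-factor comparison of cases with stroke-free pregnant controls to factors recorded routinely in both groups regardless of stroke, such as age, BMI, smoking, prior diagnoses, obstetric conditions, and the routine blood count and coagulation screen.
- Exclude work-up-dependent tests from multiple imputation in the stroke-free controls.
- Report those tests descriptively in ASPP cases, with the proportion tested shown for each group. Do not use the nonpregnant stroke group as a substitute comparator, because it is matched on stroke etiology and the antibodies may be part of that etiology.

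In Data collection and management, state whether the blood indices of Table 2 are collected in the stroke-free controls.

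The cost is wording only, with no new data. The downside is that a few laboratory factors will have no odds ratio against stroke-free controls.

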**• Medication history**
▪ Antihypertensive (if with record the duration of antihypertensive medication use, including pre-pregnancy and during pregnancy, and the types of medications, such as methyldopa, labetalol, amlodipine)
▪ Antiplatelet
▪ Oral contraceptive
• **Stroke evaluation**
▪ Type: Ischemic (thrombotic, embolic) or hemorrhagic (intracerebral, subarachnoid)
▪ Etiology
(1) Ischemic stroke (carotid stenosis, intracranial atherosclerotic stenosis, cardiogenic embolic stroke, arterial dissection, pregnancy-related hypercoagulable state, moyamoya disease)
(2) Hemorrhagic stroke (AVM, IA, pregnancy-related hypercoagulable state)
(3) Other stroke types: Cerebral venous thrombosis, cerebral sinus thrombosis, stroke caused by systemic inflammation, hematological disorders (such as thalassemia, aplastic anemia), arterial dissection (such as carotid dissection), cardiovascular diseases (such as valvular heart disease, embolism due to atrial fibrillation)
▪ Location and size: Anterior or posterior circulation, cortical or subcortical
▪ Diagnostic neuroimaging: CT, CTA, MRI, MRA, DSA, etc.
▪ Cardiac examination: ECG, echocardiography, etc.
• **Pregnancy-/puerperium-associated variables**
▪ Week of gestation and trimester at stroke onset^a^
▪ Gestational hypertension
▪ Preeclampsia/eclampsia
▪ HELLP syndrome
▪ Gestational diabetes
▪ Frequency of previous pregnancy and pregnancy-/puerperium-associated stroke
• **Data on delivery**
▪ Type: Spontaneous vaginal delivery, cesarean section, or prenatal termination (induced abortion or labor)
▪ Week of gestation at delivery
• **Stroke management**
▪ Ischemic stroke
(1) Nonsurgical treatment (if with record dose and duration): anticoagulant (heparin, warfarin), antiplatelet (aspirin, clopidogrel), intravenous thrombolysis (alteplase, tenecteplase), etc.
(2) Surgical treatment: mechanical thrombectomy, etc.
▪ Hemorrhagic stroke
(1) Nonsurgical treatment: Supportive (blood pressure control, intracerebral pressure control), etc.
(2) Surgical treatment: Open surgery (clipping for IA, excision for AVM, hematoma evacuation), endovascular intervention (coiling for IA, embolization for AVM), ventriculopuncture drainage, etc.
▪ Time relationship with terminating the pregnancy (if with surgical treatment): after, before, or during the same period
• **Complications**
▪ Neurologic: Intracerebral rebleeding (hemorrhagic stroke), vasospasm or delayed cerebral ischemia, intracerebral hemorrhage (ischemic stroke), brain herniation, etc.
▪ Systemic: Chest infection, urinary tract infection, deep venous thrombosis, pulmonary embolism, gastrointestinal bleeding, myocardial ischemia, etc.
• **Offspring-related variables**
▪ Term at birth: Pre-term, full-term, or post-term
▪ Gender
▪ Birth date
▪ Birth weight
▪ Apgar scores at 1, 5, and 10 min
▪ Transfer to NICU (if with record etiology)

*BMI* body-mass index, *NIHSS* National Institute of Health stroke scale, *mRS* modified Rankin Scale, *RBC* red blood cell, *WBC* white blood cell, *PLT* platelet, *TC* total cholesterol, *HDL-C* high-density lipoprotein cholesterol, *TT* thrombin time, *PT* prothrombin time, *FIB* fibrinogen, *APTT* activated partial thromboplastin time, *SBP* systolic blood pressure, *DBP* diastolic blood pressure, *AVM* arteriovenous malformation, *IA* intracerebral aneurysm, *CT* computed tomography, *CTA* computed tomography angiography, *MRI* magnetic resonance imaging, *MRA* magnetic resonance angiography, *DSA* digital subtraction angiography, *ECG* electrocardiography, *NICU* neonatal intensive care unit

^a^The first trimester is defined as the period from conception to 12 + 0 weeks of gestation. The second trimester spans from 12 + 1 weeks to 28 + 0 weeks of gestation. The third trimester begins after 28 + 1 weeks of gestation. Puerperium is defined as the period within 6 weeks postpartum

### Follow-up schedule

All participants will be followed up through telephone interviews. The initial follow-up is scheduled to take place between December 2024 and February 2025. The follow-up phase will consist of three rounds, each lasting 3 months and conducted every 3 years. The specific follow-up schedule is as follows:(1) First follow-up: Conducted between December 2024 and February 2025, focusing on stroke recurrence, cardiovascular health indicators, and quality-of-life assessments. During this period, any newly occurring stroke events will be documented, including the nature and severity of recurrent strokes, and changes in cardiovascular risk factors, such as blood pressure and lipid levels, will be monitored.(2) Second follow-up: Conducted between December 2027 and February 2028, continuing with telephone interviews and standardized questionnaires to assess participants’ life quality, including emotional state and daily activity capacity, while monitoring stroke and cardiovascular health status(3) Third follow-up: Conducted between December 2030 and February 2031 to further observe late-stage stroke and cardiovascular disease, particularly focusing on the increased cardiovascular risk phase post-menopause.

If participants report a stroke recurrence during the follow-up period, researchers will obtain the hospitalization records through the following process to confirm the event: First, researchers will contact the participant’s attending physician or the relevant hospital to systematically request the hospitalization records and medical information. Second, relevant medical records will be reviewed to verify the reported recurrence event, including confirmation of diagnosis, treatment course, and length of hospitalization. Additionally, if necessary, researchers will request neuroimaging assessments (such as CT or MRI) to further confirm the nature and severity of the stroke.

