#### Primary outcome

These are the following: For Aim 1, composite unfavorable outcome defined as *mRS* > 2 or EQ-5D index score < 0.7 at follow-up; for Aim 2, recurrent strokes confirmed by neuroimaging; and for Aim 3, the Apgar scores of newborns and results from Ages & Stages Questionnaires, Third Edition (ASQ-3) at follow-up.

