The assessor will conduct the mRS scoring for each patient during the follow-up period through standardized interviews and questionnaires combined with clinical observations. The assessor will use a unified mRS scoring guideline to ensure the consistency of scoring. The assessor will supervise and guide patients to take the test using the validated Chinese version of the EQ-5D5D questionnaire.

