##### Assessment process

Assessors will document changes in patients’ functional status during follow-up, including self-reported and observed capabilities in activities of daily living, to accurately evaluate functional outcomes.

Neonatal asphyxia will be assessed using Apgar scores at 1, 5, and 10 min, with scores of 8–10 defined as no asphyxia, 4–7 as mild asphyxia, and 0–3 as severe asphyxia. The assessment will be conducted by healthcare personnel trained specifically in neonatal care to ensure the accuracy and consistency of the scores.

Developmental outcomes for offspring will be assessed using the Ages and Stages Questionnaire, Third Edition (ASQ-3), which is one of the most widely used tools for screening comprehensive developmental status in children aged 1 to 66 months. The ASQ-3 categorizes developmental status into five subdomains: (1) Communication, (2) gross motor, (3) fine motor, (4) problem-solving, and (5) personal-social. Based on scores in each subdomain, results will be classified as “above,” “close to,” or “below” the threshold. The assessment will be conducted by trained assessors to ensure the reliability and accuracy of the results [14].

Recurrent stroke and stroke during subsequent pregnancy are defined as events where women experience a recurrent stroke and a stroke during a subsequent pregnancy, respectively, both confirmed by corresponding medical or insurance records. Intrauterine death or stillbirth is defined as a dead fetus in the uterus at any trimester or the birth of a dead infant after 28 + 1 weeks of gestation. Critical illness is defined as the offspring requiring hospitalization due to a diagnosed disease, including neurological diseases (such as epilepsy and cerebral palsy), cardiovascular diseases (such as congenital heart disease), gastrointestinal diseases (such as necrotizing enterocolitis), respiratory diseases (such as allergic asthma), urological diseases (such as hypospadias), hematological and immunological diseases, and other major disorders.

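### Recurrent stroke is pursued only on the woman's own report, and the Aim 1 composite does not say how a death is scored, so absolute risks can be understated

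*Protocol article*

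**What the plan says.** **Contact.** The Follow-up schedule states: "All participants will be followed up through telephone interviews". Index events run from January 2015 to November 2024. The first round of calls is December 2024 to February 2025 and the third is December 2030 to February 2031. The first call can therefore come about 10 years after the index stroke, and the last about 16.

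**Aim 2, recurrent stroke.** The trigger for looking further is in the Follow-up schedule: "If participants report a stroke recurrence during the follow-up period, researchers will obtain the hospitalization records". Under Primary outcome the endpoint is "recurrent strokes confirmed by neuroimaging". Assessment process sets another standard: recurrent stroke and stroke in a later pregnancy are "both confirmed by corresponding medical or insurance records". The Follow-up schedule asks for imaging only where it is needed.

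**Aim 1, functional outcome.** The composite is mRS > 2 or "EQ-5D index score < 0.7 at follow-up". On method, the assessment criteria after Table 3 say: "The assessor will conduct the mRS scoring for each patient during the follow-up period through standardized interviews and questionnaires". The EQ-5D is completed by the patient under the assessor's guidance.

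**Death.** Table 3 lists in-hospital mortality and long-term mortality as outcomes of their own. It asks for etiology for recurrent stroke but not for either mortality row. The definitions of the two primary outcomes do not mention death.

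**Relatives.** Table 1 lets representatives or relatives give consent, so women who have died or cannot speak for themselves can be in the cohort.

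**The concern.** Both maternal primary outcomes are written around a living woman who can answer the telephone. For Aim 2, a woman who died of a second stroke after discharge cannot report it, and the article names no other event that starts a search of records. The reference to medical or insurance records is a standard for confirming an event. It does not say that records are searched without a report. The neuroimaging requirement is a further hurdle for a woman who died before she was scanned.

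For Aim 1, neither the interview-based mRS nor the self-completed EQ-5D can be obtained from a woman who has died, and the composite does not say how she is classified. Without a rule, 36 centers may handle her differently.

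At stake are the absolute risk of an unfavorable outcome, the absolute risk of recurrence, and the prognostic model, which would lose the factors that predict death. The 20% attrition allowance and the proposal in the Discussion to add centers help precision. They do not correct a loss that is tied to the outcome.

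**Working it through.** No figure in the article rests on this point, so there is nothing to reproduce. The checks below give size and direction.

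**1. Aim 1, absolute risk.** Inputs from the article: 400 ASPP women (Abstract, Sample size estimates) and, in the Background, an "inhospital mortality rate of 4.2% for pregnant women experiencing acute stroke". Assumed: the share *s* of survivors with an unfavorable outcome, and that every in-hospital death is enrolled.

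- Expected in-hospital deaths: 0.042 × 400 = 16.8; survivors: 383.2.
- Risk with deaths counted: (s × 383.2 + 16.8) / 400. Risk with deaths left unscored: s.
- Shortfall: 0.042 × (1 − s).

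| s (assumed) | Deaths counted | Shortfall |
|---|---|---|
| 10% | 13.8% | 3.8 points |
| 15% | 18.6% | 3.6 points |
| 20% | 23.4% | 3.4 points |
| 30% | 32.9% | 2.9 points |

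Deaths between discharge and the call would add to this.

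**2. Aim 2, absolute risk.** Let *r* be the true recurrence risk and *f* the fatal share of recurrences, both assumed. If fatal recurrences are not found and those women are left out, the observed risk is r(1 − f) / (1 − rf). With r = 5%:

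- f = 5%: 0.0475 / 0.9975 = 4.8%
- f = 10%: 0.045 / 0.995 = 4.5%
- f = 20%: 0.040 / 0.990 = 4.0%
- f = 30%: 0.035 / 0.985 = 3.6%

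**3. Direction of the comparison, Aim 1.** Take s = 10% in both groups, so that leaving deaths out gives a risk ratio of 1.00. With ASPP mortality of 4.2%, the ASPP risk with deaths counted is 0.042 + 0.958 × 0.10 = 0.138. The comparator mortality is assumed:

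- 8%: comparator risk 0.172, true ratio 0.80
- 10%: comparator risk 0.190, true ratio 0.73
- 2%: comparator risk 0.118, true ratio 1.17
- 0%: comparator risk 0.100, true ratio 1.38

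If the comparator dies more often, losing deaths hides an ASPP advantage. If it dies less often, losing deaths flatters ASPP.

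**4. Direction of the comparison, Aim 2.** Assume true recurrence of 6% in ASPP and 10% in nonpregnant stroke (ratio 0.60). With the formula in step 2:

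- fatal share 10% in both groups: observed ratio 0.60
- 20% in ASPP, 10% in the comparator: 0.53
- 10% in ASPP, 20% in the comparator: 0.67

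The bias can go either way and nearly vanishes when the fatal shares are equal.

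**The case against.** **Deaths are collected.** Table 3 has mortality in hospital and in the long term, and Table 2 takes mRS and/or NIHSS at discharge from the medical record, so the in-hospital deaths can be known without a call. The composite is met by either component, so a missing EQ-5D need not block it. A unified mRS guideline is mentioned but not shown, and death is conventionally given the worst grade on that scale. This stands in part. A reader might infer that the plan drops deaths from Aim 1, but the article does not say so. It is silent, and the shortfall in the first table is conditional on deaths being left unscored.

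**Fatal recurrences might still be caught.** The first-round description says that new stroke events will be documented, relatives may consent, and nothing bars them from answering. Recurrences during the index admission should be in hospital records. It would therefore be too strong to say that a fatal recurrence can never be counted, or that it is analyzed as event-free. What remains is that the only trigger the article writes down is the participant's own report.

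**This is a condensed article.** Call scripts, cause-of-death fields and competing-risk methods commonly sit in fuller documents, and their absence here is not a fault. The trigger and the outcome definitions are different: the article does state them. An analysis plan cannot recover an event that nobody looked for.

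**Direction.** A reader might infer that ASPP will look safer than it is. That holds for absolute risk, and against the non-stroke pregnant controls if, as one would expect, their mortality is lower. It does not follow against nonpregnant stroke. The Background reports that "women with pregnancy-associated stroke have lower risks of recurrent ischemic stroke and mortality compared to those with strokes unrelated to pregnancy", which points the other way, and it adds that recurrence of intracerebral hemorrhage and of cerebral venous thrombosis does not differ significantly.

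**Conclusion.** The point holds as a defect in how events are found and outcomes defined, and it should be corrected. A recurrent stroke after discharge that kills the woman or leaves her unable to report has no stated route into the Aim 2 primary outcome. The Aim 1 composite does not state that death is unfavorable.

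The consequence that can be supported is understated absolute risk. For Aim 1 this is about 3 to 4 percentage points at survivor rates of 10% to 30%. That rests on the cited 4.2% applying to this cohort, on those women being enrolled, and on their being left unscored. For Aim 2 the size depends on the recurrence risk and fatal share, which the article does not give; at an assumed 5% risk, fatal shares of 5% to 30% bring the observed figure to between 4.8% and 3.6%.

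No direction can be asserted for ASPP against nonpregnant stroke. On the article's own expectation of lower mortality in ASPP, the loss could hide an ASPP advantage.

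**What to change.** 1. **Follow-up schedule:** let a report by the participant or a relative, of a recurrence or of the participant's death, start record retrieval. Obtain the terminal hospital or insurance record through the process already described, in all groups alike.
2. **Aim 2 outcome:** count a fatal stroke as recurrent only if it is new and distinct from the index event. Otherwise deaths from the index stroke would be counted as recurrences. Flag fatal events confirmed from records without imaging, and run a sensitivity analysis without them.
3. **Confirmation standard:** reconcile Follow-up schedule, Primary outcome and Assessment process, which now differ on whether neuroimaging or records confirm a recurrence.
4. **Aim 1 outcome:** state that death by the time of follow-up counts as unfavorable (mRS > 2).
5. **Aim 2 analysis:** treat death without recurrence as a competing event.

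The cost is a few sentences of protocol text, one question for relatives on the call, and record requests for the women who have died. The rounds in 2027–28 and 2030–31 can use the new trigger, and deaths before the first round can be traced retrospectively. The downside is small: some fatal events will rest on records without imaging.
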